## Abstract

**Introduction:**

In the face of escalating medical complexity, the development of simple strategies that allow the optimization of resources becomes more urgent than ever. This is particularly evident in cardiovascular diseases (CVD), where despite successful risk stratification and mitigation strategies, elevated mortality rates persist among socioeconomically disadvantaged groups. Efforts to prevent CVD events rely on early identification of at-risk individuals and timely implementation of risk-mitigating measures. Persistent challenges in health systems to identify and intervene with high-risk patients underline the growing importance of implementation science. Operating in the real-world context, this field allows to bridge the gap between identifying at-risk individuals and implementing tailored therapeutic strategies, facilitating the clinical assimilation of diagnostic and therapeutic advancements. RE-AIM (Reach, Effectiveness, Adoption, Implementation, Maintenance) framework was applied to structure and evaluate this implementation process.

**Methods and analysis:**

The CARDIOGAP + project emerges as a prospective solution to this challenge. By focusing on the industrial and manufacturing workforce, it seeks to achieve the early identification of high and very high-risk individuals through data routinely collected in Occupational Medicine (OM) appointments, which occur biennially (or annually for individuals aged 50 or over). Patients will be risk stratified according to the ESC guidelines using the data collected on the OM appointments, allowing a systematic and prompt recognition of individuals at elevated cardiovascular (CV) risk. The identified patients will be referred to a CV risk hospital consultation, where therapeutic interventions fostering adherence will be implemented. After the first hospital appointment, patients will be followed up to 1 year. As a pilot implementation study, sample size was determined by feasibility and precision considerations rather than by a formal power calculation for the exploratory 12-month risk-factor outcomes.

**Ethics and dissemination:**

This study was developed with reference to the SPIRIT (Standard Protocol Items: Recommendations for Interventional Trials) recommendations, adapted for a non-randomized implementation study, and in compliance with the Declaration of Helsinki and Good Pharmacoepidemiology Practice (GPP). Reporting of study results will follow the STROBE guidelines, ensuring ethical conduct and data integrity. Written informed consent will be obtained from all participants or their legal representatives. Confidentiality is safeguarded through de-identification and secure data storage. Results may be published or shared in public databases, following Novartis and ICMJE standards.

## Introduction

1

Cardiovascular diseases (CVDs) remain the leading causes of death and disability worldwide and substantially contribute to loss of health and increasing health system costs. Several environmental, metabolic, and behavioral risk factors, including air pollution, high blood pressure, high levels of low-density lipoprotein cholesterol (LDL-C), kidney disfunction, tobacco smoking, among others, contribute to the development and establishment of CVD (1).

Atherosclerosis, a chronic inflammatory condition characterized by recruitment of white blood cells to the arterial wall, subsequent accumulation of lipids, and ultimate lesion formation, is the main pathophysiological process underlying clinical CVD (2). With time, the atherosclerotic plaque can become more fibrous and accumulate calcium mineral. Advanced atherosclerotic plaques can invade the arterial lumen, impeding blood flow and leading to myocardial infarctions (MI), stroke, and peripheral artery disease (3).

Atherosclerotic cardiovascular disease (ASCVD) incidence and mortality rates are declining in many countries in Europe, but it is still a major cause of morbidity and mortality (4). In fact, mortality data demonstrate that CVD remains the main cause of death in the European region. Furthermore, it is also important to acknowledge that there are important disparities across the different countries in the European region, as well as in the burden of CVD between men and women (5). Cardiovascular disease led to an annual toll of over 3.8 million deaths throughout Europe, comprising nearly 1.76 million deaths in men and exceeding 2 million deaths in women. This constituted 39% of all male deaths and 46% of all female deaths. In contrast, cancer, the second most prevalent cause of death in Europe, contributed to 24% of all male deaths and 20% of all female deaths (5). Although more women than men die from CVD in the region, higher age-standardized mortality and deaths in those aged <70 years demonstrate that CVD remains a greater burden among men in all countries. This observation substantiates the advocacy for alleviating the cardiovascular disease burden and mitigating disparities by instituting focused, evidence-driven interventions for both treatment and prevention across all Europe. In Portugal, atherosclerotic cardiovascular disease (ASCVD)-related costs amount to 1% of the Gross Domestic Product (6). In 2015, around 12% of the Portuguese population aged between 40 and 65 had a very high risk of developing a fatal cardiovascular event within the next 10 years. Thus, correctly identifying people with an elevated CV risk, at an early stage and the adoption of appropriate preventive strategies, is an important step to reduce CVD mortality in the Portuguese population (7).

While effective therapeutic strategies exist, much remains to be done in applying current knowledge more effectively and equitably in practice (3).

The development of simple strategies that allow the optimization of resources becomes more urgent than ever, particularly those focused on personalized problem solving through procedures that assure the clinical integration of diagnostic and therapeutic innovations. The use of preventive therapies in at­ risk individuals will likely demonstrate high cost­ effectiveness from a societal perspective (3). Implementation science, which tests, in the real world, the ability of health systems to deliver healthcare, is of increasing importance in this setting. To structure and evaluate this process, the present protocol adopts the RE-AIM framework (Reach, Effectiveness, Adoption, Implementation, Maintenance), a widely used implementation science framework for pragmatic, real-world health system interventions (8). RE-AIM dimensions are mapped onto the study's objectives in Section 2.1.3.

Considering CVD, it is essential to prevent the cardiovascular (CV) event from occurring, through the identification of individuals at risk and the early implementation of measures that mitigate this risk (9).

Despite the relatively easy identification of patients at risk and the effective therapies that exist, many of these patients end up entering the hospital not for the outpatient consultation, but through the emergency room with the CV event already established. This is, in many cases, due to the difficulty of the health system to identify and act on patients at greatest risk (10).

CARDIOGAP + proposes to provide an integrated response to this challenge, through:
the early identification of patients at risk among those working at the industrial and manufacturing workforce, using data usually obtained in the Occupational Medicine (OM) consultation, as OM appointments are mandatory and take place every 2 years, or yearly for patients who are 50 or over, which allows for a regular follow-up of workers and an early and timely identification of patients at greater CV risk, even those that usually do not go to the Primary Care Physician and,the protocolization of referral to a hospital consultation, in a low-bureaucracy way upon the identification of very high CV risk patients by the OM physician who will refer the patient to the CV risk appointment where effective therapies that enhance therapeutic adherence will be thoroughly implemented.In summary, CARDIOGAP + favors intervention strategies with several stakeholders aligned on a single mission: using the available resources and routinely collected data, and taking advantage of these existing, yet underused, mechanisms of referral to improve and promote the referral of very high CV risk patients to a CV risk appointment, thereby implementing simple and pragmatic strategies that cost-effectively avoid events, creating value for patients before they become ill.

## Methods and analysis

2

### Objectives

2.1

CARDIOGAP + aims to identify patients with elevated CV risk at OM consults and evaluate the effectiveness of the intervention (i.e., a simplified referral process of these patients by the OM of industrial/manufacturing companies for a cardiovascular risk hospital consultation) in CV health, through the assessment of the proportion of in-hospital consultation participation, adherence to therapy and the medium-term impact on risk factors.

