#### Secondary objectives

2.1.2

Secondary objective 1: To assess the effective referral rate of identified patients with elevated CV risk in OM to the CV risk hospital consultation.Secondary objective 2: To assess the rate of hospital CV risk consults that effectively took place after the referral by the OM physician.Secondary objective 3: To measure the performance of the simplified referral process for a CV risk consultation, through the assessment of therapeutic adherence, and impact on the CV risk profile 12 months after the intervention.Secondary objective 4: To estimate the levels of Lipoprotein (a) in patients.Secondary objective 5: To estimate the prevalence of CV risk factors in workers in the industrial/manufacturing companies in the municipality of São João da Madeira, using the AHA Life's 8 system.Secondary objective 6: To assess the effective referral rate of patients to the primary care consultation.Secondary objective 7: To assess the effective application of the implementation strategies in the CARDIOGAP + project.

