#### Implementation science framework

2.1.3

This protocol is informed by the RE-AIM framework (Reach, Effectiveness, Adoption, Implementation, Maintenance), used to plan and evaluate pragmatic, real-world health system interventions. Primary and secondary objectives relate to RE-AIM dimensions as follows: Reach is addressed through the proportion of eligible OM attendees identified and screened (secondary objectives 1–2); Effectiveness is addressed through change in CV risk profile at 12 months (secondary objectives 3–4); Adoption is addressed through the referral rate by OM physicians and participating companies (secondary objectives 1 and 6); Implementation is addressed through fidelity to the referral protocol and consultation attendance (secondary objectives 2 and 7); and Maintenance, while outside the 18-month observation window of this pilot, will be discussed qualitatively as a direction for future, longer-term evaluation.

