#### Destination

2.2.12

These variables are related to the referral given to the participant after the clinical evaluation. At the baseline, the OM doctor indicates whether advice was given, referred to Family Medicine, or to a hospital; at T12, the hospital medical doctor indicates whether participant was discharged or continue with hospital follow-up.

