6. Level of Adherence to Medication Prescribed in the Hospital CV Risk Consultation: Descriptive statistics will assess the adherence levels, measured by SMAQ among patients prescribed medications in the hospital CV risk consultations.
7. Proportion of Patients Who Attended Smoking Cessation Consultation: Descriptive statistics will determine the proportion of patients attending smoking cessation consultations over patients who were referred and participated in hospital CV risk consultation.
8. Change in distribution from Baseline in Various CV Risk Factors after 12 Months: Appropriate statistical methods will be used to calculate the distribution change from baseline (first hospital consultation) for the following CV risk factors after the use of this simplified referral process.
a. LDL-C
b. Blood pressure (SBP and DBP)
c. Moderate or severe chronic kidney disease
d. Smoking status
e. HbA1c
f. BMI
Statistical methods for this endpoint are specified in Section 2.3.1.
9. Distribution of Lipoprotein (a) at the first hospital consult: Descriptive statistics will assess the distribution of Lipoprotein (a) at the first hospital consult.
10. Prevalence of CV Risk Factors in the industrial/manufacturing in São João da Madeira: Appropriate statistical methods will be used to estimate the prevalence of CV risk factors within the industrial/manufacturing companies, including the levels of Lipoprotein (a) among very high CV risk individuals.
11. Proportion (%) of Identified Patients Referenced to GP Consultation: Descriptive statistics will be used to calculate the percentage of patients referred to GP consultations.

For the change in CV risk factors from baseline/T0 to T12, repeated continuous measures will be analyzed using linear mixed-effects models (or generalized estimating equations, as appropriate to the outcome distribution) with a random intercept per participant to account for within-subject correlation across the baseline, T0 and T12 assessments. Binary or categorical repeated measures will be analyzed using generalized estimating equations with a logit link. Models will be adjusted *a priori* for age, sex, baseline CV risk category, and baseline value of the outcome variable; additional covariates identified as clinically relevant confounders may be added in sensitivity analyses.

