### Strengths and limitations

2.4

CARDIOGAP + relies on a low-bureaucracy referral pathway designed for real-world adoption using mandatory occupational health infrastructure to screen a working-age population often missed by primary-care-based cardiovascular screening. In this context, three main limitations should be noted: Possible underestimation of true population-level risk (a “healthy worker effect”) due to restricting enrollment to currently employed individuals (since unemployed, informally employed, retired, and long-term sick-leave workers may carry a higher CV risk burden); Absence of power for a confirmatory test of 12-month risk-factor change (exploratory outcome); Barriers to hospital consultation adherence, which may be limited by shift workers’ difficulty attending hospital appointments, transportation constraints, low risk-perception among asymptomatic individuals, and gaps in OM-hospital communication

However, it should be noted that the low-bureaucracy design partially mitigates all these constraints and limitations, and their impact will be assessed empirically (secondary objectives 1, 2, 3, 7).

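### The aim, secondary objective 3 and the RE-AIM Effectiveness line credit an uncontrolled 12-month change to the referral process, and section 2.4 does not list this as a limitation

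*Protocol article*

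**What the plan says.** The causal wording appears in three places in the protocol article, and the endpoint table leans the same way.

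- Section 2.1 (Objectives) aims to "evaluate the effectiveness of the intervention (i.e., a simplified referral process of these patients by the OM" physician, judged by consultation attendance, adherence and medium-term impact on risk factors.
- Section 2.1.2, secondary objective 3: "To measure the performance of the simplified referral process for a CV risk consultation, through the assessment of therapeutic adherence", together with "impact on the CV risk profile 12 months after the intervention".
- Section 2.1.3 (RE-AIM): "Effectiveness is addressed through change in CV risk profile at 12 months (secondary objectives 3–4").
- Table 3, endpoint 8, takes the first hospital consultation as baseline and measures change "for the following CV risk factors after the use of this simplified referral process".

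On design, section 2.2.4 limits the T0 and T12 assessments to participants whom the OM doctor referred. Section 2.3.1 fits repeated-measures models with a random intercept per participant, or generalized estimating equations, adjusted for age, sex, risk category and baseline value. It describes the change as running from baseline/T0 to T12 and uses the OM baseline, T0 and T12 assessments.

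Section 2.2.2 calls these analyses exploratory and hypothesis-generating, and intends them to inform the design and sample size of a later evaluation. Section 2.4 states that "three main limitations should be noted": the healthy worker effect, lack of power for 12-month change, and barriers to attendance.

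**The concern.** Effectiveness and impact of a referral process mean a difference from what would have happened without it. Nothing in the plan estimates that. Everyone followed to T12 took the pathway, so no model term can separate the pathway from elapsed time, and adding confounders does not change this.

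Other care is built into the setting. Under section 2.2.12, "the OM doctor indicates whether advice was given, referred to Family Medicine, or to a hospital", and referral to primary care is itself secondary objective 6 and endpoint 11. Those who reach T12 also chose to attend.

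Two things are at stake. A fall in LDL-C or blood pressure could be read as an effect of the process when part or all of it has other causes. And section 2.2.2 passes the result on to the planning of a larger study. Required sample size varies with the inverse square of the assumed effect, so a planning effect inflated by background change would leave that study too small.

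**Working it through.** **1. The plan's own figure.** Section 2.2.2 gives a 2.2% margin for a prevalence of 15% in 1000 persons at 95% confidence. Check: 1.96 × √(0.15 × 0.85 / 1000) = 0.0221, so it reproduces. It concerns prevalence only; no planning figure exists for the 12-month change.

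**2. What the change contains.** Claim and design side by side:

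| Component of the change | Separated by the plan? |
|---|---|
| Referral process | No: every modelled patient took it |
| OM advice, primary care | No: no group with these alone is followed |
| Time trend | No: no parallel series |
| Selection of attenders | No: non-attenders have no T12 |
| Regression to the mean | Largely, if T0 is the reference; not if the OM value is |

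**3. Regression to the mean.** Table 1 refers some workers on a single high OM value, for example LDL-C above 190 mg/dL. Endpoint 8 starts at T0, a fresh measurement, which removes much of the effect. The baseline/T0 wording in section 2.3.1 leaves open whether the selecting OM value becomes the reference. If it does, the expected fall with no intervention is

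SD × (1 − r) × φ(k) / (1 − Φ(k)), with k = (cut-off − mean) / SD,

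where r is the test-retest correlation. The documents give no mean, SD or r, so these are assumptions: LDL-C mean 130, SD 35 mg/dL, hence k = (190 − 130) / 35 = 1.71. For the top 15% of any normal marker, the fall in SD units is (1 − r) × φ(1.036) / 0.15.

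| r | LDL-C fall (mg/dL) | Top 15% (SD) |
|---|---|---|
| 0.9 | 7.4 | 0.16 |
| 0.8 | 14.9 | 0.31 |
| 0.7 | 22.3 | 0.47 |
| 0.6 | 29.7 | 0.62 |

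This applies to a marker that itself triggered referral. Workers referred on SCORE or SCORE2, which also depend on age and smoking, would show less in any one marker.

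**4. Could routine OM visits act as a control?** The Introduction says "OM appointments are mandatory and take place every 2 years, or yearly for patients who are 50 or over". Section 2.2 gives 6 months of enrolment plus 12 of follow-up, 18 in all.

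- Aged 50 or over, enrolled at months 0 to 6: next visit at months 12 to 18, inside the window, the last with no slack.
- Under 50: next visit at months 24 to 30, outside it.

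Size, assuming 20–50% of 1000 are aged 50 or over, 15–30% of those are referred and 60–80% of the referred attend:

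- Referred non-attenders: 1000 × 0.2 × 0.15 × 0.2 = 6 up to 1000 × 0.5 × 0.30 × 0.4 = 60.
- Not referred: 1000 × 0.2 × 0.70 = 140 up to 1000 × 0.5 × 0.85 = 425.

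The difference detectable with 80% power, (1.96 + 0.84) × √(1/n₁ + 1/n₂), is 0.47 to 1.28 SD for attenders against non-attenders (90 v 60; 24 v 6), and 0.30 to 0.69 SD against workers not referred (120 v 350; 18 v 170).

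**The case against.** The strongest reply is that this is an openly non-randomized pilot whose primary objective is to implement a process, and that an uncontrolled before-after comparison is a legitimate choice for it. The 12-month analyses are labelled exploratory. Section 2.1 judges effectiveness partly by attendance and adherence, which are simple descriptive measures. Endpoint 8 says after the use of the process, which is temporal wording. Usual and newly prescribed drugs are recorded separately at T0 and T12, so background treatment is partly visible. The Introduction says that the population includes workers who usually do not see a primary care physician, so how much their treatment changes outside the pathway is unknown.

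Most of this stands, and it limits the point to wording and interpretation; the design itself need not change. It does not remove the point. Exploratory and unpowered describe precision, and a larger uncontrolled sample would carry the same bias. The words effectiveness, performance and impact are attached to the process in sections 2.1, 2.1.2 and 2.1.3, and section 2.4 is silent on the gap.

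A reader might go further and infer that the yearly OM visits of workers aged 50 or over would supply the missing comparator. The documents do not support that. Workers under 50, who can be referred under the SCORE2 criterion, have no second OM visit in the window. Workers who meet the criteria are meant to be referred, so those left with OM data alone are either a few self-selected non-attenders or workers below the thresholds. Change between two OM visits would also restart from the selecting measurement, so regression to the mean in attenders would look like benefit beside workers not selected for high values.

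Nor do the documents show that any improvement will be announced as proven effectiveness. They show only that the objectives are worded to invite that reading.

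**Conclusion.** The point holds as a mismatch between claim and design. The T0-to-T12 change is an uncontrolled within-patient change among referred workers who attend, and it cannot be credited to the referral process. This conclusion follows from the documents alone. The size of the bias does not: the 0.16 to 0.62 SD and the 7.4 to 29.7 mg/dL rest on assumed distributions and test-retest correlations, and apply only if the OM value is the reference. No size can be given for background care, time trend or self-selection. The primary objective, the referral and attendance proportions and the prevalence estimates are not affected.

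**What to change.** 1. Reword the effectiveness part of the aim in section 2.1, secondary objective 3, the Effectiveness line in section 2.1.3 and endpoint 8 in Table 3 as: *within-patient 12-month change from T0 among hospital attenders, not attributable to the referral process*.
2. In section 2.3.1, replace the baseline/T0 wording so that the reported change is from T0 to T12, as endpoint 8 already defines it.
3. Add the missing comparator and regression to the mean to the limitations in section 2.4.
4. State in section 2.2.2 that this change is not to be used as the expected effect of the process when the future evaluation is sized.

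The cost is text only, with no new data, visit or test.

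Collecting the next annual OM record of workers aged 50 or over is optional and not part of the required fix. Under the assumed age shares it means 200 to 500 extra records (20–50% of 1000) from company sites, with consent amended to cover them, because section 2.2.4 plans OM data at baseline only. If done, it should be reported as a small, non-equivalent descriptive comparison.
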